#### 2.5.2. Health-Related Fitness

Health-related fitness will be assessed by the following tests: 6-min running test, 6-min walking test (used only in 5–6 year-old children, first grade), Harre test, standing long jump test and shuttle run 4 × 10.

The 6-min running test (6MRT), derived from Cooper’s 12-min test, consists of performing the maximum running distance possible, also walking when tired, for a time of 6 min. At the end of the test, the meters covered in the given time are considered. The test is validated for preschool [34] and school-aged children [35]. The 6-min walking test (6MWTs) was conducted using ATS guidelines (2002) [36]. All children will receive the same instructions before undertaking the walk test. The children are asked to walk up and down at their best pace but not to run or race. The children will be explained that it was not a competition. During the performance, no indications such as “Slow down” or “Go faster”, were given, except for encouragement (e.g., “You are doing great” and “Keep going”) [37,38]. Only 5–6 year-old children from the whole sample performed this test, as it is easier and more adaptable to this age group. Both the 6 MRT and the 6 MWT are a reliable test to assess the cardiorespiratory fitness in children.

Standing long jump (SLJ) or standing broad jump is a good test to assess lower body strength, and it could be considered as a general index of upper and lower body muscular fitness in youth [39,40]. The participant stands behind the starting line, with feet together, and pushes off vigorously and jumps forward as far as possible. The distance is measured from the take-off line to the point where the back of the heel nearest to the take-off line lands on the mat or non-slippery floor. The test will be repeated twice, and the best score retained (in cm).

The Harre circuit (HC), a dexterity’s test, is a timed instrument based on simple and dynamic movements repeated in three spatial directions: right, forward and left [41,42,43].

The shuttle run 4 × 10 test (4 × 10 SRT) [44] measures agility, speed and coordination while running between two lines drawn on the floor 10m apart to pick up small blocks. The children ran as fast as possible from the starting line to the other line and return to the starting line, crossing each line with both feet every time. This test will be performed twice, covering a distance of 40 m (4 m × 10 m). Each time the children crosses any of the lines, he/she had to pick up (the first time) or exchange (second and third time) a sponge that is previously placed behind the lines. The stopwatch is interrupted when the children cross the end line with one foot.

#### 2.5.3. Motor Control Development During Fine and Gross (Locomotor) Tasks

Gross- and fine-motor competences will be assessed using an instrumented approach based on wearable inertial sensors [45,46]. The selected instrumented approach allows the quantitative analysis of motor competence characteristics (e.g., automaticity, complexity and regularity) and their longitudinal monitoring as related to age and/or motor development.

For gross-motor competence 3 inertial sensors (OPAL; APDM: Portland, OR, USA) will be attached, using elastic Velcro bands, to the lower shanks (above lateral malleolus) and lower back (at L5 level) of each child over clothes, and 3D acceleration and angular velocity is acquired from each sensor during natural and tandem gait along a 15 m straight path. Each child walks 3 times back and forth normally (for a total of 45 m) and 1 time in tandem (along the straight line, positioning the heel of the front foot in contact with the toes of the back one), prior to data collection, all participants are allowed to perform a tentative trial (10 TW strides) to ensure they understand the tandem gait instructions.

For the assessment of fine-motor competence, the 3 inertial sensors (OPAL; APDM: Portland, OR, USA) will be attached to the wrists (dorsal aspect) and lower back (at L5 level), and 3D accelerations and angular velocity will be acquired during the Placing bricks test [47]. Each child, sitting at a desk, attached 18 1 × 2 Duplo bricks one at a time onto a 6 × 12 Duplo plate using one hand, then the other for the second trial; blocks will be positioned on the side of the plate corresponding to the hand to be used, while the opposite hand was kept on the table or used to stabilize the plate according to child’s preference. For all trials data are acquired at 128 Hz sampling frequency.

Temporal parameters, variability, regularity, motor complexity, stability and rhythmicity calculated from acquired motion and represented in a graphical polar plot [46] allow one to qualitatively characterize different areas of motor control performance.

#### 2.5.4. Dietary Patterns

The ZOOM-8 study [48] is conceived to investigate more in depth the dietary habits and physical activity of Italian primary school children, and the role of the health services in geographic areas with different levels of childhood overweight and obesity, as shown in the Italian surveillance system named “OKkio alla SALUTE”.

In the ZOOM-8 study, the anthropometric measures of children are taken and their parents fill in two questionnaires, one general questionnaire including general information along with lifestyle questions (i.e., amount of physical activity, time spent at the screen, sleeping hours, family composition, etc.) and a semiquantitative food frequency questionnaire (FFQ), built up following the methodology described and validated by Willett [49], consisting of 53 commonly used food items categorized into 11 food groups [50].

We will use the same two questionnaires, asking the children’s parent participating in the study to complete them and providing specific instructions on filling them in at home. Frequency response categories for all food portions ranged from the number of times per day, per week, per month, per year to never. Manufactured products will be reported as number (or fraction) of units consumed.

#### 2.5.5. Anthropometric Evaluation

Six anthropometric characteristics (height, weight, waist and hip circumferences, triceps and subscapular skinfold thicknesses) will be collected according to standardized procedures [51,52]. In particular, height is measured to the nearest 0.1 cm using a portable stadiometer (SECA 217, SECA: Hamburg, Germany). Body weight is measured to the nearest 0.1 kg (light indoor clothing, without shoes) using a calibrated electronic scale (SECA 877: Hamburg, Germany). Waist circumference (WC) and hip circumference (HC) are measured to the nearest 0.1 cm with a non-stretchable tape (GPM measuring tape; DKSH Switzerland Ltd.: Zurich, Switzerland): WC is measured between the lowest rib and the iliac crest and HC at the widest part of the hip. Triceps (TSF) and subscapular (SSF) skinfold thickness is measured to the nearest 0.1 cm on the left side with a Lange caliper (Beta Technology Inc.: Santa Cruz, CA, USA). TSF is measured midway between the tip of the acromion and olecranon processes, while SSF raising an oblique skinfold below the inferior angle of the scapula at 45° to the horizontal plane following the natural cleavage lines of the skin. TSF and SSF were evaluated according to the Frinsancho cutoff (2008) [53].

BMI will be calculated as weight (in kilograms) divided by the square of height (in meters). This index will be used to assess the weight status of each participant according to Cole cutoff values by sex and age [54,55]. Consequently, we will calculate the BMI z-score.

Waist/height ratio (WtHR) will be calculated and children will be stratified into two categories (≤0.5 and >0.5); the value of 0.5 is chosen as the cut-off of cardiovascular risk [56,57,58].

Body composition parameters (percentage fat (%F), fat mass (FM) and fat free mass (FFM)) will be calculated using the skinfolds equations of Slaughter et al. (1988) [59] and the cutoff for %F by Laurson (2011) [60] is used to identify subjects with lower or higher than recommended values.

#### 2.5.6. Sociodemographic Determinants.

Parents or guardians will fill out a questionnaire (inside the ZOOM8 Questionnaire) [49,50] about sociodemographic factors (e.g., sex, age, birth date, place of birth and type of work) as well as their habitual PA and sedentary habits.

#### 2.5.7. Cognitive Function

Two cognitive tasks will be administered: one task investigates the executive functions (i.e., working memory), which are sensitive to exercise, the other investigates multisensory perception.

Verbal working memory will be assessed by means of the backward digit span, a subtest of the Wechsler intelligence scale for children (WISC-IV) [61]. The task involves the verbal presentation of digit series and requires children to repeat the series in reverse order. The score will be calculated as the highest number of correct digits remembered.

Multisensory perception will be investigated using the sound-induced flash illusion, SIFI [62,63]. The SIFI consists of the illusory perception of two flashes when one flash is presented simultaneously with two (beep) sounds. Susceptibility to the SIFI is considered an indicator of efficient multisensory processing [64,65,66]. In this task, 1 or 2 flashes (the number of which has to be reported) is presented together with 1 or 2 task-irrelevant sounds. Different multisensory congruent (1flash/1beep, 2flashes/2beeps) or incongruent (1flash/2beeps) conditions are presented. The stimulus onset asynchrony (SOA) varies amongst trials (with SOAs of 70, 110, 150 and 230 ms) in the 1flash/2beeps and 2flashes/2beeps conditions.

#### 2.5.8. Time-On-Task Behavior

We will structure a self-administered active breaks questionnaire for teachers to monitor a possible change in the behavior of the children. The teacher’s questionnaire will include different domains regarding the satisfaction, the feasibility, the effectiveness and the organizing of the ABs. The questionnaire will include items investigating potential changes in the time-on-task behavior, attention and wellbeing of the children, and their personal attitude in handling, implementing and performing ABs. We also perform a children’s self-administered active breaks questionnaire to explore satisfaction, feelings and pleasure in performing ABs.

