## Abstract

Background: Children and adolescents should perform, according to the World Health Organization guidelines, at least 60 min of moderate-to-vigorous physical activity per-day in order to avoid the risk of metabolic and cardiovascular diseases. The school represents a fundamental setting to conduct interventions to promote physical activity (PA) and contrast sedentary behaviors. Active breaks (ABs), bouts of 10 min of PA conducted inside the classroom, seem to be a good strategy to promote PA and improve classroom behavior. The aim of this study protocol is to describe the design and the assessment of the Imola Active Breaks I-MOVE study. Methods: The I-MOVE study is a school-based intervention trial, with a quasi-experimental design, performed in a primary school. It involves one experimental-group performing the intervention, focused on ABs, and one control-group. Nine main outcomes are evaluated: PA and sedentary behaviors; health related fitness; motor control development; dietary patterns; anthropometric evaluation; sociodemographic determinants; cognitive function; time-on-task behavior and quality of life. Conclusions: Results from the I-MOVE study will help to clarify the effects of incorporating ABs in the Italian school curriculum as a new public health strategy and an innovative school model oriented to the well-being of children and teachers for the best quality of school life.

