### Aims of the I-MOVE Study

1. To evaluate the effects of an active breaks intervention in increasing total day and school day PA and reducing time spent in sedentary habits in children attending primary school; the relationship between objective and reported measures of PA and health-related fitness will be examined.

2. To assess the possible effect of active breaks in improving quality of life in children, stratified by anthropometric evaluation, diet habit, socioeconomic status and parent-perceived children’s quality of life.

3. To investigate the effects of active breaks as a strategy to change the time-on-task behavior and the cognitive function of children (executive functions and multisensory perception).

4. To investigate the possible effects of active breaks in improving the development of fine and gross motor control, quantified using wearable sensors.

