### 2.5. Data Collection and Outcome Measures

During the Imola Active Breaks Study the following outcomes will be evaluated: (1) PA and sedentary behaviors; (2) health related fitness; (3) motor control development during fine and gross (locomotor) tasks; (4) dietary patterns; (5) anthropometric evaluation; (6) sociodemographic and early determinants; (7) cognitive Function; (8) time-on-task behavior and (9) quality of Life.

As shown in Table 2, all the measurements will be evaluated at baseline T0 (October 2019) and will then be assessed at mid-intervention T1 (October 2020) and at the end of the intervention T2 (June 2021) to investigate group differences and changes over time. The process evaluation will performed 6 months after the end of the intervention T3 (December 2021.)

The comparisons between T0, T1 and T2 will allow the research to determine the timing of any long-term effect of ABs and whether the effects of ABs are cumulative in time or reach a ceiling after T1 (for example, if there are cumulative effects, then performance should reveal a pattern T0 < T1 < T2; by contrast, if they reach positive effects in a few months and then stabilize, then performances at T1 and T2 should not differ).

Moreover, we planned an assessment at the mid-intervention to measure an acute effect before the daily active breaks and immediately after the 10-min bout for cognitive and time on task outcomes. During this specific mid-intervention we will monitor the amount of PA performing an active break, 10 min thrice a day, during a school day for a week. This assessment will be focused on cognitive function and time-on-task behaviors, since these could be more affected after acute exercises than chronic ones, as shown for some cognitive functions in the literature [24,25,26].

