## Figures and Tables

**Figure 1 ijerph-17-06123-f001:**
[figure not shown]
Flow chart of the I-MOVE study.

**Table 1 ijerph-17-06123-t001:** Components of I-MOVE protocol.

Phase	Aim	Examples of the Type of Exercises	Duration
Warm-up	Cardiorespiratory and mobility exercises	“The chair march”: The children all stand up and move their chairs sideways, waiting for the teacher’s commands. They begin to march, raising their knees well and resting their toes on the chair, without pushing upwards. Progressively, they also combine the movement of the legs with the alternating movement of the arms.	2 min
Tone-up	High-intensity interval training (HIIT) exercises	HIIT Animal jumps: Children scattered around the classroom have to jump like frogs for 40 s then rest for 20 s and repeat the exercise 2 times, then they jump like kangaroos for 40 s with 20 s break to be performed 2 times.	5 min
Cool-down	Breath and relaxation exercises	The imaginary balloon: Children must inflate an imaginary balloon by inhaling and exhaling, mimicking the progressive expansion of the balloon with the widening of their arms. We ask for a very slow and long exhalation twice as long as the inspiration.	3 min

**Table 2 ijerph-17-06123-t002:** The Imola Active Breaks Study data collection and outcome measures.

Outcome Measures	Baseline October 2019 (T0)	Mid-Intervention October 2020 (T1)	End of Intervention June 2021 (T2)	6 Months After End of Intervention December 2021 (T3)
Personal information (Age, Country)	√		√	
PA and sedentary behavior (accelerometer)	√	√	√	
Total reported physical activity Questionnaire	√	√	√	
Health related fitness	√	√	√	
Motor control development	√	√	√	
Dietary patterns	√	√	√	
Anthropometric evaluation	√	√	√	
Sociodemographic and early determinants	√		√	
Cognitive Function	√	√	√	
Time-on-task behavior (Teachers and children self-administrated questionnaire)		√	√	
Quality of Life	√	√	√	
Process evaluation focus group with children				√
Process evaluation: focus group with teachers				√

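### Time-on-task behavior: text and Table 2 disagree on a baseline, and the only instrument described has no evident control-class equivalent, so a controlled, baseline-adjusted longer-term effect cannot be estimated as written

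*Protocol article*

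**What the plan says.** The abstract states "Nine main outcomes are evaluated", and time-on-task behavior is on that list. Aim 3 is "To investigate the effects of active breaks as a strategy to change the time-on-task behavior and the cognitive function of children".

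On timing, section 2.5 refers to Table 2 and says that "all the measurements will be evaluated at baseline T0 (October 2019"), with repeats at T1 (October 2020) and T2 (June 2021). In Table 2 the row "Time-on-task behavior (Teachers and children self-administrated questionnaire") is ticked at T1 and T2 only.

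On the instrument, section 2.5.8 says: "We will structure a self-administered active breaks questionnaire for teachers to monitor a possible change in the behavior of the children". Of its content it says that the "questionnaire will include different domains regarding the satisfaction, the feasibility, the effectiveness and the organizing of the ABs", and it adds items on possible changes in time-on-task, attention and wellbeing. The children's questionnaire covers how much they liked the breaks.

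Section 2.5 also announces an acute assessment at mid-intervention, "before the daily active breaks and immediately after the 10-min bout for cognitive and time on task outcomes". Section 2.6.1 plans to compare the two groups on change from baseline to follow-up by ANOVA and ANCOVA. Section 2.6.2 says that qualitative analysis will support the evaluation of time-on-task.

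**The concern.** An effect on children's behavior over two school years, in a non-randomized study, needs three things: a value before the breaks start, the same value later, and both of these in classes without breaks. For time-on-task the schedule in Table 2 lacks the first. The instrument in section 2.5.8 does not evidently supply the third, because a questionnaire about how the breaks went, and what changed with them, has no natural meaning for a teacher who never ran one.

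If the plan is followed as written, the information on this outcome comes from teachers who volunteered for the intervention, deliver it, and are asked how well it works. That is useful process information. Reported under aim 3 as an effect of the breaks, it would carry more weight than it can bear.

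**Working it through.** No arithmetic applies: the plan gives no effect size, standard deviation or sample size for time-on-task. Section 2.3 sizes the study on accelerometer data (48 per group, 96 in total), and nothing here depends on that figure. The check sets the sections side by side.

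**1. Schedule.** Table 2 has 13 rows. Two are the T3 focus groups. The other 11 compare as follows.

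| Rows in Table 2 | T0 | T1 | T2 |
|---|---|---|---|
| Accelerometer, reported activity, fitness, motor control, diet, anthropometry, cognition, quality of life (8 rows) | yes | yes | yes |
| Personal information, sociodemographic determinants (2 rows) | yes | no | yes |
| Time-on-task (1 row) | no | yes | yes |

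Time-on-task is the only one of the 11 without a baseline tick. The sentence in section 2.5 says that everything is measured at T0 and cites this same table. Both cannot be right. The sentence is loose elsewhere too, since two rows skip T1, so it may be a general summary. That does not settle which statement holds for time-on-task.

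**2. Would adding a T0 tick be enough?** Not with the instrument in section 2.5.8. Its domains concern the breaks, and its behavior items ask about change. Before the breaks have begun, a teacher can report neither. The empty T0 cell is therefore consistent with the instrument, and correcting the table alone would not produce a usable baseline.

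**3. Control classes.** Section 2.5.10 describes control-group teachers as having chosen not to perform the breaks. No version of the questionnaire for them is described, and the children's questionnaire has no time-on-task content that could stand in. The same items would not mean the same thing in the two groups.

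**4. Who rates.** Section 2.2 reports that ten teachers of 5 classes out of 15 agreed to take part and were trained. Assuming that these ten deliver the breaks, as their training implies, the teacher data would be the views of about ten unblinded volunteers on their own intervention.

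**5. Against the analysis.** The comparison in section 2.6.1 needs a baseline and a follow-up value in each group. From steps 1 to 3, a usable baseline is missing and a comparable control value is not evident. The reasoning in section 2.5 on cumulative or ceiling effects, which looks for a pattern across T0, T1 and T2, meets the same obstacle for this outcome.

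**The case against.** The strongest reply has five parts.

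- **The acute assessment.** Section 2.5 plans a before-and-after assessment around a single break. A reader might infer from the points above that no effect of any kind on time-on-task can be estimated. The documents do not support that: the acute assessment could give a short-term, within-class contrast, although no control comparison for it is stated. A reader might also infer that the teacher questionnaire is to be used there and could not register a change over ten minutes. Section 2.5 names no instrument for this assessment, and section 2.7 refers to an operation manual describing all instruments, so this is no finding.
- **Qualitative analysis.** Section 2.6.2 gives the outcome partly to qualitative methods, and section 2.6.1 does not list the outcomes it covers. This stands as a caution: the authors may not intend an ANCOVA of time-on-task. Aim 3 is nevertheless worded as an effect, which qualitative reports from the break classes cannot establish.
- **The baseline.** Saying flatly that there is none would take one side of a contradiction. That is fair, and the point is put here as a conflict to reconcile.
- **Control teachers.** Section 2.5.8 does not restrict the questionnaire to break classes. True, so the absence of a control measurement is not proven. What is established is that the content described has no evident counterpart there.
- **Importance.** The nine main outcomes include sociodemographic determinants, so the phrase lists domains rather than confirmatory endpoints, and accelerometry is the primary measure. This limits the weight of the point but does not remove it.

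Nor can the matter be left to an analysis plan: the article itself fixes the instrument's content and timing, and no analysis can supply measurements that were not collected.

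**Conclusion.** The point holds in a limited form. Section 2.5 and Table 2 contradict each other on whether time-on-task is measured at T0, and section 2.5.8 describes no measure that teachers of both groups could complete on equal terms. As written, a controlled, baseline-adjusted longer-term effect cannot be estimated for this outcome, and the teacher data amount to perceived change reported by self-selected teachers who deliver the breaks.

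Its extent is one of nine main outcomes and part of one of four aims. The accelerometer outcome and the other measured outcomes are untouched. The conclusion assumes that the questionnaire in section 2.5.8 is the measure behind the Table 2 row, as the row label suggests, and that no break-neutral version for control teachers exists in a document not shown. If such a version exists and is used at T0, only the conflict between text and table remains.

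**What to change.** 1. Reconcile section 2.5 with Table 2, stating when time-on-task is measured.
2. Split the teacher questionnaire. Add a short block of class behavior and attention ratings that does not mention breaks, completed by teachers of both groups at T0, T1 and T2, and compare the groups on it. Report the items about the breaks (satisfaction, feasibility, perceived effectiveness) descriptively, for the break classes only.
3. If T0 is no longer possible, collect the block at T1 and T2 and report it as a post-only comparison without baseline adjustment, stating that it is open to confounding by teacher self-selection and to unblinded rating. Unblinded rating by the teachers who deliver the breaks remains a limitation even with a T0 value.
4. If the block is not adopted, relabel the outcome as teacher-perceived change, treat it as process or acceptability data, and reword the time-on-task part of aim 3 to match.

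The cost of item 2 is a few questionnaire items per time point. For control-class teachers this is a new though small task: the only role the article describes for them is the T3 focus group, so their agreement is needed. Item 4 costs only wording.
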